### Sensitivity analyses

Due to the slow rate of accrual, it may not be possible to achieve the recruitment target of 75 participants per arm in the recruitment timeframe. In addition, we may not be able to achieve the projected effect size. If we observe any lack of statistical power, we will use bootstrap techniques to compute the bootstrap confidence intervals for the effect estimates and report them.

The analyses will be performed on an ITT basis, meaning all participants randomised to art psychotherapy or usual care will be included in the analysis. During data entry, validations have been written into the system to minimise the amount of missing data, however, missing data may still occur. The frequency and percentage of missing values will be reported overall and by arm.

Missing data will be investigated for cause and extent, and multiple imputations with the assumption of missingness at random (MAR) will be considered. Analyses will be conducted to assess the assumption of MAR and identify baseline variables to be used in the imputation models. Missing observations in the primary and secondary outcomes will be replaced by imputed values using the predictive mean matching method in chained equations [39, 40] of linear regression. At least 20 datasets will be created for the imputation of each outcome, and the imputation-specific estimates for the effect of intervention on the primary and secondary outcomes will be combined using Rubin’s rules [41].

These analyses will be considered as sensitivity analyses, as the analyses will be conducted with missing observations replaced by the imputed values and the results will be compared with the complete case and ITT analyses.

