### Sample size

The primary objective is to assess the effectiveness of art psychotherapy in reducing the frequency and severity of aggressive behavior in adult secure care as measured by the Modified Overt Aggression Scale (MOAS) [16]. Based on the results of the feasibility study [11], we assumed a minimum clinically important difference (MCID) of 5 points on the MOAS scale, a common standard deviation of 10 points in the control and intervention groups, and a correlation of 0.25 between the baseline and post-treatment MOAS scores. In addition, we may need to account for clustering by therapist, as a single therapist will apply the intervention to more than one patient. We assumed that each site would have a minimum of 2 therapists and the intraclass correlation (ICC) of the MOAS scores for the same therapist would be 1% in the intervention arm. Under these assumptions, 80% power and a type I error rate of 5%, 59 participants would be required in each arm. To account for an assumed attrition rate of 20%, this figure is inflated to a final sample size of 75 participants per arm, yielding a final sample size of 150 participants.

This would also allow the study to detect a change of 0.5 points on the Brief Symptom Inventory (BSI) Positive Symptom Distress Index (PSDI), used to evaluate changes in patient distress related to psychiatric symptoms [17]. Using an estimated SD of 0.8, the sample size calculated above would result in a power greater than 90% for the BSI comparison.

If the target recruitment (sample size) is not achieved, we will use sensitivity analysis with appropriate statistical methods as planned in the statistical analysis section. If the effect size (i.e. the mean difference of change in MOAS and its standard deviation) differs from our assumptions used in the sample size calculation, this may affect the power/sample size as shown in Table 1.

**Table 1 Tab1:** Potential effects of differing effect sizes and standard deviations on the sample size

Effect size	Power	SD	Method	Correlation (baseline and follow-up)	Alpha	Sample size (per arm)	Final sample size (inc. 20% dropout)
4	0.8	10	ANCOVA	0.25	0.05	92	230
6	0.8	10	ANCOVA	0.25	0.05	41	103
5	0.8	8	ANCOVA	0.25	0.05	37	93
5	0.8	12	ANCOVA	0.25	0.05	85	213

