The study has found it harder to recruit participants than anticipated and has led to a slower recruitment rate. An 80% power was approved by the NIHR and resulted in a reduction in the required sample size. However, it is anticipated that the study may not achieve the current target sample size of 75 participants per arm. Due to the smaller sample size, we could have wider confidence intervals, reflecting greater uncertainty about the true effect size; as such, results may need to be interpreted with this in mind. However, we have planned to use bootstrap techniques to compute the bootstrap confidence intervals for the effect estimates and report them.

For the economic analysis, the primary HRQoL measure for estimating QALYs is the self-reported, adapted EQ-5D-3L. The rationale is that the self-reported, adapted EQ-5D-3L best aligns with the current NICE methods for technology appraisal guidelines and has been developed specifically for people with learning disabilities. However, there are complications within this patient population that might mean that although NICE prefers the EQ-5D-3L and the adapted version has face validity in the patient population (i.e. those with learning disabilities), it might not be the most appropriate measure to use for the economic analysis; therefore, psychometric analyses are proposed to inform the preferred outcome for the economic analyses. The use of psychometric analyses means the choice of outcome measure for the economic analysis will be chosen post-hoc (albeit, the psychometric analyses will be completed before conducting the economic evaluation); however, as post-hoc choices can allude to data/outcome mining (e.g. making the results fit the preferred outcome), this post-hoc choice does not change the primary outcome for the economic analyses which will remain the adapted, self-reported EQ-5D-3L. Rather, the psychometric analyses results will be published alongside the economic analyses, with the economic analyses results, discussion and conclusion informed by the psychometric analyses to suggest which outcome measure has the best psychometric performance and therefore may be the more ‘appropriate’ outcome for the economic analysis, despite the primary outcome remaining the adapted, self-reported EQ-5D-3L.

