## Trial status

The final version of this analysis plan was approved by the trial steering committee on the 04/02/25. The first patient was enrolled on the 05/05/2023, with the last participant expected to complete follow-up on the 12/04/2025 (± 2 weeks).

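### Bootstrap intervals hang on an undefined, possibly result-dependent lack of power and are offered against a recruitment shortfall, where they add neither power nor precision

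*Protocol article*

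**What the plan says.** The Sample size section sets the design. On the target difference it says: "we assumed a minimum clinically important difference (MCID) of 5 points on the MOAS scale". The planning SD is 10 in each arm, and scores before and after treatment are taken to correlate at 0.25. From these it concludes that, with "80% power and a type I error rate of 5%, 59 participants would be required in each arm", rising to 75 per arm for attrition. It adds that if the target is missed, a sensitivity analysis by suitable methods will be used, and refers the reader to the statistical analysis section. Table 1 shows how the required size changes with the effect and the SD.

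The Sensitivity analyses section opens with two risks: that 75 per arm may not be recruited, and that the effect may fall short of the one projected. Its response is: "If we observe any lack of statistical power, we will use bootstrap techniques to compute the bootstrap confidence intervals for the effect estimates".

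The Discussion reports slow recruitment and says "it is anticipated that the study may not achieve the current target sample size of 75 participants per arm". It accepts that intervals may then be wider and that this bears on interpretation. The next sentence opens with a contrasting word and says that bootstrap intervals are planned.

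Trial status gives the dates: "The final version of this analysis plan was approved by the trial steering committee on the 04/02/25", the first enrolment on 05/05/2023, and the trial "with the last participant expected to complete follow-up on the 12/04/2025" (± 2 weeks).

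**The concern.** There are two faults.

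- **The remedy does not fit the problem.** A shortfall in participants is a shortfall in information. A bootstrap re-uses the participants already in the data. It can give an interval that depends less on normality, but it cannot recover the power or precision lost with the missing participants.
- **The trigger is open.** Power is fixed by design inputs and is not something observed in the data. The section does not say how a lack of power would be recognised. Because it counts a smaller effect than projected among the causes, the decision to compute a second interval can depend on the primary result. That sits badly with a plan whose stated aim is to limit data-driven analysis.

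At stake is how a null or borderline primary result is read. A second, slightly narrower interval could appear beside the first because the first disappointed, while the precision actually available goes unstated.

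**Working it through.** **1. The plan's own figure.** Inputs from Sample size: difference 5, SD 10, correlation 0.25, power 80%. Two-sided 5% follows from Statistical principles, and 1:1 allocation from Randomisation. With the ANCOVA variance factor 1 - 0.25² = 0.9375:

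n per arm = 2 × 100 × 0.9375 × (1.96 + 0.8416)² / 5² = 58.87, so 59. This matches the plan. Attrition: 59 / 0.8 = 73.75, so 74, against 75 stated. The sample size is not in dispute.

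**2. Power and precision at smaller analysed numbers.** SE = 10 × √(2 × 0.9375 / n); power = Φ(5/SE - 1.96); half-width = 1.96 × SE.

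| Analysed per arm | SE | Power for 5 points | 95% CI half-width |
|---|---|---|---|
| 59 | 1.78 | 80% | 3.5 |
| 50 | 1.94 | 73% | 3.8 |
| 40 | 2.17 | 64% | 4.2 |
| 30 | 2.50 | 52% | 4.9 |

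At the assumed 20% attrition, 40 analysed per arm corresponds to 50 randomised per arm (50 × 0.8).

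**3. What a bootstrap does to this.** Simulated ANCOVA trials with the same inputs, 1,000 per setting, 399 resamples within arm, percentile interval, no therapist clustering. Skewed errors were gamma with shape 0.5, which is an assumption. Each cell gives model interval / bootstrap interval.

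| Per arm | Errors | Power | Type I error |
|---|---|---|---|
| 60 | normal | 78.3% / 80.2% | 5.7% / 6.2% |
| 60 | skewed | 80.1% / 79.6% | 4.8% / 7.1% |
| 40 | normal | 62.2% / 65.3% | 5.3% / 6.1% |
| 40 | skewed | 65.0% / 66.6% | 4.7% / 7.0% |
| 30 | normal | 51.8% / 55.4% | 5.0% / 6.7% |
| 30 | skewed | 55.3% / 57.6% | 4.2% / 7.7% |

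Power changes by -0.5 to +3.6 percentage points. The bootstrap interval is about 3-5% narrower (for example 9.65 against 10.11 points in full width at 30 per arm, normal errors), and its type I error is higher in every setting. The small apparent gain therefore comes with extra false positives. Simulation error is about 1.6 points for power and 0.7 for type I error, so single normal-error cells are weak evidence; the pattern across settings is the point.

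**4. The trigger.** Suppose, since the plan does not define it, that observed power means power at the estimated effect. Then it is Φ(|z| - 1.96), where z is the test statistic. Any non-significant result has |z| < 1.96 and hence observed power below Φ(0) = 50%. Observed power stays below 80% until |z| reaches 1.96 + 0.84 = 2.80. On this reading the trigger is a restatement of the p-value, and every non-significant result sets it off.

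**5. Dates.** Final assessments are at 38 weeks ± 2 (Timing of outcome assessments).

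- If 12/04/2025 is a week-38 visit, the last randomisation was about 20/07/2024 (06/07 to 03/08/2024 with the window), some 28 weeks before approval on 04/02/2025.
- If it were a week-19 visit, the last randomisation was about 30/11/2024.
- The 20 recruitment months given under Trial design, counted from 05/05/2023, end about 05/01/2025.

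All three fall before approval.

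**The case against.** The strongest reply is that this concerns a sensitivity analysis only. Analysis of primary outcome specifies a mixed model and a 95% CI from it, Statistical principles sets the significance criterion, and the bootstrap sits under the heading Sensitivity analyses. That stands: the structure already implies that the model-based interval is primary, and a reader who infers that the bootstrap would replace it goes beyond the text. What is missing is an explicit statement. It is worth adding because bootstrapping is also listed under Alternative methods if distributional assumptions not met, which is a separate and legitimate use.

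Four further inferences are tempting and should not be drawn:

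- **That the plan claims the bootstrap restores power.** It nowhere says so, and the Discussion openly warns of wider intervals. The fault is that the bootstrap is placed as a counterweight to that warning.
- **That the Sample size section prescribes a bootstrap.** It refers only to suitable methods in a sensitivity analysis.
- **That the stated 80% is not the trial's power.** The number enrolled is not given, and attrition could be lower than assumed. As an illustration, 65 randomised per arm with 10% loss leaves 58.5 analysed and 79.8% power by the formula above. Keeping the design calculation in an analysis plan is also normal.
- **That the document states recruitment had closed.** It does not. Closure is inferred from dates, and the July 2024 figure depends on reading 12/04/2025 as a week-38 visit.

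**Conclusion.** The concern holds in a limited form. Making bootstrap intervals conditional on an observed lack of power is unsound: the condition is undefined, it can depend on the primary result, and the remedy adds neither power nor precision. At 30 to 60 analysed per arm the percentile interval tends to be slightly too narrow, with type I error of about 6-8%, subject to the simulation's assumptions.

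The loss that the bootstrap cannot repair ranges from none at 59 analysed per arm to power of 52% and a half-width of 4.9 points at 30, almost the whole 5-point difference of interest. Where the trial lies in that range cannot be told from the document. On every reading of the dates randomisation had ended by about January 2025, so the number should have been available when the plan was approved. The sample-size calculation and the model-based primary analysis are not in question here.

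**What to change.** 1. In Sensitivity analyses, delete the sentence that makes the bootstrap conditional on a lack of power.
2. In Discussion, delete the sentence that offers bootstrap intervals after the warning about wider intervals. Keep the warning.
3. State explicitly that the model-based 95% CI defined under Analysis of primary outcome decides the primary conclusion.
4. If a bootstrap interval is kept, compute it whatever the result, label it a sensitivity analysis, and justify it on distributional grounds, as the section on alternative methods already does.
5. Give the number randomised, the number expected to be analysed, and the power and CI half-width for 5 points at that number under the existing assumptions.

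The cost is a few sentences and one line of calculation, with no new participants, data or change to the primary model. The restated power may be lower than 80%, depending on the number analysed.

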### Timing of outcome assessments

Outcome assessments (Table 2) are conducted at baseline (prior to randomisation), 19 and 38 weeks post-randomisation with a ± 2 weeks window.

**Table 2 Tab2:** Schedule of enrolment, interventions, and assessments

Procedures	Screening	Baseline	Randomisation	Treatment phase	19 weeks	Weekly	38 weeks	Ad hoc
Informed consent	X							
Eligibility assessment	X							
LDSQ	X							
Treatment allocation			X					
Demographics		X						
Medical history		X						
Q1 HONOS (WAA or LD)	X							
Randomisation		X						
Delivery of intervention				X				
Compliance				X				
MOAS		X			X	X	X	
EQ-5D-3L self-reported LD adapted version*		X			X		X	
EQ-5D-3L Proxy Version 1		X			X		X	
Resource use					X		X	
ReQoL-10 Self Report version		X			X		X	
ReQoL-10 Proxy reported**		X			X		X	
BSI		X			X		X	
Adverse event assessments								X
Physician’s withdrawal checklist								X

*LDSQ* Learning Disability Screening Questionnaire, *Q1 HONOS (WAA or LD)* Item 1 of the Health of the Nation Outcome Scale (Working Age Adults or Learning Disabilities), *MOAS* Modified Overt Aggression Scale, *BSI* Brief Symptom Inventory

*EQ-5D-3L self-reported using LD (learning disabilities) adapted version

**ReQoL-10 Self-Report version completed by a proxy

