### Primary outcome

The primary outcome is the frequency and severity of aggressive incidents as measured by the Modified Overt Aggression Scale (MOAS) at week 19 post-randomisation.

The MOAS is completed by a research nurse or clinical support officer at baseline (prior to randomisation), and weekly from week 19 to week 38 post-randomisation, and if necessary, checking with a member of the ward team to ensure that it accurately reflects the participant’s behaviour. The MOAS is not always completed by the same research nurse/clinical support officer, so we are recording who has conducted each assessment.

The MOAS is a validated observer-rated measure that assesses the frequency and severity of aggressive incidents among people with ID over the past week (ICC = 0.93 [16]). The scale consists of four categories: verbal aggression, aggression against property, auto-aggression (against self), and physical aggression (against others). Each category will be scored using a 5-point scale (0 = no events within that category, 4 = most severe form of aggression within the category). The rater selects as many items as are appropriate. The items in each category are summed. The summed scores are multiplied by the severity weight for that category (verbal aggression × 1, aggression against property × 2, auto-aggression × 3, physical aggression × 4). The weighted scores are summed to obtain the total MOAS score, with a higher score indicating more aggressive behavior [16]. Thus, the primary outcome is a change in the MOAS score from baseline to week 19 post-randomisation.

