### Analysis of primary outcome

The aim of the primary analysis is to examine the effectiveness of art psychotherapy in reducing the frequency and severity of aggressive incidences compared to usual care, as measured by the change in MOAS score from baseline to week 19 post-randomisation. The distribution of the MOAS scores will be assessed graphically using histograms and the mean (SD) or median [IQR] of the change in score from baseline to week 19 will be tabulated overall and by trial arm (art psychotherapy versus usual care). The change of primary outcome from baseline to week 19 will be assessed graphically using a scatter plot.

The primary outcome analysis will be performed on an ITT basis. Initially, we will use a linear mixed-effect regression model [27, 28], with the week-19 MOAS score as the dependent variable and the randomisation group as the independent variable, adjusted for the baseline MOAS score, random effect of the variable indexing strata based on gender and diagnosis of psychosis. In addition, we anticipate potential clustering in the intervention arm due to therapists. We will examine this by the ICC from the linear mixed-effect model and if there is a considerable amount of heterogeneity in the primary outcome associated with therapists, we will adjust the effect estimate for the partial clustering due to therapists. For this, both partially homoscedastic and heteroscedastic regression models will be explored, and we will report the results as appropriate. The homoscedastic model assumes between-cluster variability is only present in the intervention arm and the individual level variation is the same in both arms. The heteroscedastic model assumes between-cluster variability is only present in the intervention arm but allows different individual level variation in intervention and control arms [29, 30]. From the initial model(s), we will present the estimated difference in MOAS score at week-19 for the intervention group compared to the control group with 95% CI.

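### The only predictors named for imputing a missing week-19 MOAS are baseline variables, although the MOAS is also collected at weeks 20 and 21, inside the assessment window

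*Protocol article*

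**What the plan says.** - **Endpoint.** Under Primary outcome, the article defines aggression "as measured by the Modified Overt Aggression Scale (MOAS) at week 19 post-randomisation". The form records the "frequency and severity of aggressive incidents among people with ID over the past week".
- **Schedule.** The same section has the MOAS completed at baseline and then "weekly from week 19 to week 38 post-randomisation". Timing of outcome assessments places the visits at "19 and 38 weeks post-randomisation with a ± 2 weeks window". Table 2 lists the 19-week and the weekly MOAS in separate columns.
- **Primary model.** Analysis of primary outcome specifies a linear mixed-effect model "with the week-19 MOAS score as the dependent variable and the randomisation group as the independent variable", adjusted for baseline MOAS. No other weekly score enters.
- **Missing data.** Sensitivity analyses says that multiple imputation under missing at random will be considered, and that analyses will "identify baseline variables to be used in the imputation models". It continues: "Missing observations in the primary and secondary outcomes will be replaced by imputed values using the predictive mean matching method in chained equations". At least 20 datasets are to be created for each outcome, and the results are classed as sensitivity analyses.
- **Strength of the baseline score.** Sample size assumes "a correlation of 0.25 between the baseline and post-treatment MOAS scores".

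**The concern.** The primary model has one post-baseline value per participant. Anyone without a week-19 score therefore contributes nothing to the treatment estimate unless the score is imputed. The imputation text points to baseline variables, and the plan's own correlation makes baseline MOAS a weak predictor.

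A participant who missed the week-19 form but was rated one or two weeks later has a recent reading of the same scale, from the same observer-rated process and within the stated window. That reading is the natural auxiliary variable. It should predict the missing score better, and it makes missing at random easier to defend than conditioning on pre-treatment information alone. The plan gives no instruction to use it. The Discussion already expects recruitment to fall short of 75 per arm, so information that is already collected is worth using.

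**Working it through.** **Is there an overlap?** Week 19 is day 19 × 7 = 133, and ±14 days gives days 119 to 147. Weeks 20 and 21 are days 140 and 147, both inside. Week 38 is day 266, with window days 252 to 280. Weeks 36 and 37 are days 252 and 259, both inside. Each form looks back one week, so these are separate readings.

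**Reproducing the plan's figure.** Inputs from Sample size: difference 5, SD 10, r = 0.25, 80% power, 5% type I error (two-sided, as under Statistical principles).

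n per arm = 2 × [10 × (1.960 + 0.842) / 5]² × (1 − 0.25²) = 62.79 × 0.9375 = 58.87, rounded up to 59, as stated. Then 59 / 0.8 = 73.75, rounded up to 74, close to the stated 75. Therapist clustering is left out below. With ICC 0.01 and an assumed 16 therapists (8 sites × 2), it moves n only to about 60 or 61.

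**Variance explained by baseline MOAS.** 0.25² = 6.25%.

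**Variance explained with the week-20 and week-21 scores added.** The documents give no week-to-week correlation ρ, so it is assumed over a range, equal for every pair of weeks, with baseline correlating 0.25 with each weekly score.

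- Correlation between weeks given baseline: a = (ρ − 0.0625) / 0.9375.
- Share of the remaining variance explained by two later scores: p = 2a² / (1 + a).
- Total R² = 0.0625 + 0.9375 × p.

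For ρ = 0.5: a = 0.467, p = 0.297, R² = 0.341.

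**Power of the imputed analysis.** With 75 randomised and 20% missing, 60 per arm are observed and 15 are missing. Let q be the share of the 15 who have both later forms. Then

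effective n = 1 / [(1 − p)/60 + p/(60 + 15q)]

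power = Φ(5 / √(2 × 100 × 0.9375 / n) − 1.96).

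With no auxiliary, n = 60: 5 / √3.125 = 2.828, and Φ(0.868) = 80.7%.

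| ρ (assumed) | p | R² | n, q = 0.25 | Power | n, q = 1 | Power |
|---|---|---|---|---|---|---|
| 0.3 | 0.102 | 15.9% | 60.4 | 81.0% | 61.3 | 81.5% |
| 0.5 | 0.297 | 34.1% | 61.1 | 81.4% | 63.8 | 83.1% |
| 0.7 | 0.550 | 57.9% | 62.0 | 82.0% | 67.4 | 85.0% |
| 0.9 | 0.843 | 85.3% | 63.1 | 82.7% | 72.2 | 87.3% |

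The gain runs from 81.0 − 80.7 = 0.3 points to 87.3 − 80.7 = 6.6 points. With only one of the two later forms available, the range is 80.9% to 87.0%. If all missing participants are true dropouts (q = 0), power stays at 80.7%.

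**The case against.** A reader might infer that observed in-window scores are set aside. The documents do not say so. The window can be read as letting a week-20 or week-21 form count as the 19-week assessment. Naming baseline variables does not say that only they will be used. The weekly MOAS is itself a secondary outcome, so a chained-equations model could include it. This objection stands: the text is silent, not prohibitive. Silence still leaves the better predictor unnamed where the plan does name predictors, and creating datasets for each outcome does not suggest a joint model across outcomes.

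A reader might also infer that a weak imputation model damages the primary result. It does not, because imputation is a sensitivity analysis that will only be considered.

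Nor do the documents support power falling to about 77% or 73% through losing 5 or 9 of the 59 per arm. Those cases leave 54 or 50 of 75 observed, which is 28% or 33% missing, beyond the 20% already allowed for.

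Three further points stand. The 6% is for baseline MOAS alone, and other baseline variables may add to it. A week-20 or week-21 score describes a different week, so it is a proxy. Several of the listed reasons for loss to follow-up, such as moving outside the clinical team's care or refusing contact, describe people unlikely to have later forms.

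Finally, rules for choosing among in-window forms are often left to a fuller document, and on its own that omission would not be a point. The imputation predictors differ, because the article, which presents itself as the detailed analysis plan, does address them.

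**Conclusion.** The point holds as an improvement to the stated imputation method. The plan names only baseline predictors, and on its own r = 0.25 the baseline MOAS is a weak one. Closer readings of the same scale are already scheduled.

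The likely size is modest: about 0.3 to 6.6 power points over 80.7% in the imputed analysis, and nothing for true dropouts. The upper end needs a weekly correlation of 0.9 and both later forms from every missing participant. The range rests on an assumed correlation of 0.3 to 0.9, equal between all weeks, and on a quarter to all of the missing having those forms. The documents give neither quantity. The calculation also treats missingness as ignorable and the imputation as efficient. The sample size is unaffected.

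**What to change.** In Sensitivity analyses, say that the imputation model for a missing week-19 MOAS will contain, alongside the baseline variables and with treatment arm, a small set of post-baseline MOAS auxiliaries. These could be the week-20 and week-21 scores, or a short summary such as the mean of the first few weekly scores after week 19. Do the same with weeks 36 and 37 for a missing week-38 score. Keep the set short: all of weeks 20 to 38 would be 19 correlated scores against about 60 observed participants per arm, which risks an unstable model.

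Also state that where several forms fall in the window, the one closest to the nominal date is analysed, and whether a week-20 or week-21 form may serve when the week-19 form is missing. If it may, the summary of later weekly scores is the more useful auxiliary for those still missing.

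The cost is a few sentences and slightly more imputation work, with no new data. The downsides are that a later score is a proxy for a different week, and that only participants with intermittent misses benefit.
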